### Primary and secondary outcomes

The primary outcome of this study is self-rated pain and discomfort in five body areas, measured using the APHIRM toolkit survey [46] administered at baseline and 12 months later.

The secondary outcomes of this study are:The level of self-rated exposure to work-related physical hazards, measured using a survey administered at baseline and at 12 months.The level of self-rated exposure to work-related psychosocial hazards, measured using a survey administered at baseline and at 12 months.

### Power and sample size

The cluster design requires the formation of intervention and control work groups containing eligible participants, from which a cluster of participants is then formed. To inform the design of the study, the distribution and number of registered paramedics assigned to stations in the two largest regions in the organisation was reviewed, by examining human resources data. As a result, the mean cluster size (number of expected participants per cluster) for this study was set at 18. This value was then used to calculate the sample size. Whilst all efforts will be made during the study to achieve this mean cluster size, the authors recognise that some clusters will have higher or lower numbers of participants due to a variety of factors, including the size of the work group at commencement and the survey response rate. The number of eligible participants in ambulance stations was found to vary considerably; from a few to more than 40. Excluding small stations from the study or grouping them together to increase the number of eligible participants may seem attractive, however these options required careful consideration. The option to exclude small stations was discarded, to avoid ethical concerns. The option to group small stations will be used to facilitate inclusion, but will be limited, because an intervention led by two managers (OICs) does not mimic the real world and introduces a potential confounding variable. A similar survey was administered with a large cohort of paramedics in Australia and achieved a 38% response rate [19] and a survey of Danish ambulance officers about the physical and psychosocial aspects of their work achieved a 62% response rate [32]. This study is anticipated to result in a high response rate because of the detailed contextualisation to suit the organisation and the current interest of the workforce in WMSDs. The attrition rate was set at 30% based on the response rate of paramedics to similar surveys [19, 32] and a protocol for a workplace intervention study in an emergency service organisation [57]. If the mean cluster size deviates significantly from the estimated value of 18, this will be identified and accounted for in the statistical analysis and the interpretation of results.

Table 1 sets out the sample size and power calculations for primary and secondary outcomes evaluated in the RCT taking into account the cluster design at Alpha = 0.05 and Power = 0.80, ICC = 0.05, mean cluster size = 18 and estimated cluster variation = 0.5625. The results of a previous study that administered an earlier version of the APHIRM survey to a cohort of workers including paramedics were used to estimate the effect size for pain/discomfort, exposure to physical hazards and exposure to psychosocial hazards [20]. A recent study involving high-risk workers, reported a relationship between the physical and the psychosocial hazard profile derived from APHIRM survey responses and the musculoskeletal pain/discomfort scores [54]. A conservative approach was taken by choosing a flat intra-cluster correlation coefficient (ICC) of 0.05. ICCs for outcome variables are generally lower than this [58]. Calculations were done using the software R (v4.0.1) [59], with results cross checked against the National Institutes of Health research methods tools [60] in the case of continuous variables.

**Table 1 Tab1:** Sample size and power calculations

	Mean	SD	Effect size (d)	Required standard sample size (N)	Required sample size accounting for cluster design (N)	Required sample size after allowing for 30% attrition
Pain/discomfort	14.9	8.3	4	136	317	412
Exposure to physical hazards	3.7	0.6	0.5	46	107	139
Exposure to psychosocial hazards	2.4	0.6	0.5	46	107	139

The required sample size for the intervention arm, accounting for this cluster design was calculated and the sample size was then increased by 30% to allow for attrition at 12 month follow up. Based on the outcome ‘pain/discomfort’ at an effect size of four, we need to recruit a minimum of 18 clusters of 18 or more participants into the trial (*n* = 317/18 = 17.6 clusters; in practice, nine intervention and nine control clusters). For the outcomes ‘exposure to physical hazards’ and ‘exposure to psychosocial hazards’ at an effect size of 0.5, we would recruit a minimum of six clusters of 18 or more participants into the trial (*n* = 107/18 = 5.9 clusters; in practice three intervention and three control clusters). This study aims to recruit 18 clusters (nine intervention and nine control) of 18 or more participants from one region of the organisation to allow for potential attrition.

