### Recruitment of survey participants

Following randomisation into the trial of six work groups, a list of all eligible study participants will be extracted from the organisation’s human resources information system by the approved data custodian. The list will be provided to the WHSP facilitator, who will contact the OIC of each work group and initiate the planning for the survey. Planning includes checking the participant details, agreeing on survey timing and developing communication strategies. The OIC will be advised of their allocation to either intervention or control work group at this time. Although this means the OIC is not blinded to allocation prior to the conduct of the survey, it is considered an important ethical consideration to explain the extent of involvement in the study to the OIC, so that expectations and their personal workload can be managed.

At a time mutually agreed by the OIC and the WHSP facilitator, the APHIRM survey invitation will be sent by email to all eligible participants in the work group. Participants will be invited to complete the online survey via a link in the email to the survey (unique to the work group) with the Participant Information Consent Form (PICF) attached. Participants who submit the survey will be implied to have consented. If participants do not wish to complete the survey, they have the option of skipping all questions. In the organisation, paramedics are provided with an organisational tablet device. Eligible participants who choose to participate will complete the survey during work time on the device. Testing has been undertaken by the organisation to ensure that the survey works on the device and meets security protocols. The survey takes 10–15 min to complete. The identity of individual participants who choose to complete the survey will not be known to the WHSP facilitator, as the survey is anonymous and participation is voluntary. The survey will be open for two weeks, to ensure different shift patterns are captured. However, this timeframe may be extended to meet operational requirements and achieve the required mean cluster size of 18 (survey responses). The WHSP facilitator will be able to monitor the number of responses from a work group during the period the survey is open through the APHIRM portal and provide reminders to the work group and feedback to OICs. OICs will be actively involved in promoting survey uptake, as would be the case in usual practice.

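### Table 1 multiplies by 1.3 where a 30% loss needs division by 0.7, and the planned 18 clusters of 18 contain almost no attrition allowance

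*Protocol article*

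**What the plan says.** All of this is in the protocol article, mostly under Power and sample size.

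- Design inputs: "Alpha = 0.05 and Power = 0.80, ICC = 0.05, mean cluster size = 18 and estimated cluster variation = 0.5625".
- Table 1, primary outcome (mean, SD, difference, individual N, clustered N, N after attrition): "Pain/discomfort 14.9 8.3 4 136 317 412". Physical hazards: "Exposure to physical hazards 3.7 0.6 0.5 46 107 139". The psychosocial row has the same three sample sizes as the physical row.
- How the allowance is applied: "the sample size was then increased by 30% to allow for attrition at 12 month follow up".
- Where the 30% comes from: "The attrition rate was set at 30% based on the response rate of paramedics to similar surveys", "and a protocol for a workplace intervention study in an emergency service organisation [57". Shortly before this: "A similar survey was administered with a large cohort of paramedics in Australia and achieved a 38% response rate". A Danish ambulance survey is given as 62%. The authors expect a high response in their own study but give no figure.
- Number of clusters: 317/18 = 17.6, rounded to nine per arm. The section closes by describing 18 clusters of at least 18 participants as recruited with attrition in mind.
- What 18 counts: Recruitment of survey participants lets the survey window be extended to "achieve the required mean cluster size of 18 (survey responses").

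**The concern.** Three things do not fit together.

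1. An N that must survive a 30% loss is N/0.7, not N x 1.3. The last column of Table 1 therefore does not deliver what its heading promises.
2. The cluster count is taken from the column before attrition, yet the text says the recruitment target allows for attrition. A reader will believe the trial has a cushion for its primary outcome.
3. The 30% is linked to response rates that correspond to 62% and 38% non-response. Those are also a different quantity from loss between two time points. The surveys are anonymous and go to everyone eligible in the work group at each wave, so no individual is followed. The loss that matters is non-response at each survey.

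At stake is whether the power claimed for pain/discomfort still holds if responses fall as the authors themselves allow for.

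**Working it through.** **Inputs** (Power and sample size, Table 1): SD 8.3 and difference 4 for pain/discomfort; SD 0.6 and difference 0.5 for the hazard scores; alpha 0.05 (two-sided assumed; the sidedness is not stated), power 0.80, ICC 0.05, mean cluster size m = 18, cluster variation 0.5625 (read as the squared coefficient of variation, CV²), nine clusters per arm, 30% loss.

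**Step 1: reproduce the plan's figures.**

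- Individual N per arm = 2 x (1.96 + 0.8416)² x (SD/difference)². Pain: 67.6, so 68 per arm and 136 in total. Hazards: 22.6, so 23 per arm and 46 in total. Both match.
- Design effect = 1 + [(CV² + 1)m − 1] x ICC. With CV² = 0.5625 it is 2.356, giving 320 and 108. With CV² x 17/18 it is 2.328, giving 316.6 and 107.1, which match 317 and 107.
- Attrition column: 317 x 1.3 = 412.1 and 107 x 1.3 = 139.1. Both match the table. Division by 0.7 does not reproduce them.

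**Step 2: test the column against its own heading.**

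| Outcome | Needed | Table 1 | Left after 30% loss | N/0.7 |
|---|---|---|---|---|
| Pain/discomfort | 317 | 412 | 412 x 0.7 = 288 | 452.9, so 453 |
| Each hazard score | 107 | 139 | 139 x 0.7 = 97 | 152.9, so 153 |

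The corrected figures are about 10% higher (453/412 = 1.10; 153/139 = 1.10).

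**Step 3: see which N sets the trial's size.**

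- 317/18 = 17.6 clusters: the figure used.
- 412/18 = 22.9 clusters; 453/18 = 25.2 clusters: neither is used.
- 18 x 18 = 324, which exceeds 317 by 7 (about 2%) and falls short of both 412 and 453.
- For the hazard outcomes 324 exceeds 153, so the gap concerns pain/discomfort only.

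**Step 4: power with 18 clusters if responses fall 30%.** Mean responses 18 x 0.7 = 12.6 per cluster (about 227 in total), design effect with CV² = 0.5625, SE = 8.3 x √(2 x DE/(9m)), single time point.

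| Responses per cluster | DE | SE | 4/SE | Power, t on 16 df | Power, normal |
|---|---|---|---|---|---|
| 18 | 2.356 | 1.416 | 2.83 | 76% | 81% |
| 12.6 | 1.934 | 1.533 | 2.61 | 69% | 74% |

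The two methods must be kept apart. The protocol's 80% corresponds to the normal column. The t column is lower even at a full 18 responses, because there are only 18 clusters.

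**Step 5: the basis of the 30%.** 1 − 0.38 = 62% and 1 − 0.62 = 38%. Neither is 30%. The third source cited carries no figure in the article.

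**The case against.** The strongest reply is that the 1.3 slip changes nothing in the trial: neither 412 nor 453 determines how many work groups are recruited. That is true. It limits the arithmetic error to a misstated column, but it also exposes the second problem, that the planned size does not contain the allowance the text claims. One could add that the target is 18 or more per cluster, so larger clusters might supply a margin. The article gives no figure for this, and 18 is the mean used throughout.

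Two stronger readings are tempting, and the document supports neither.

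- *That the true loss is 38% to 62%, so 30% is wrong.* The quoted rates are non-response in other surveys, not loss between this trial's two waves. The 30% also rests on a third source whose figure is not shown, and the authors give reasons to expect a better response (tailoring to the organisation, tablet access, completion in work time, a short survey). The 30% is poorly explained, not shown to be wrong.
- *That 18 is a staff headcount, so responses would average about 11 or 7 per cluster (18 x 0.62 = 11.2; 18 x 0.38 = 6.8).* Human resources data informed the 18. However, Power and sample size defines it as expected participants, Recruitment of survey participants as survey responses, and Quantitative analysis defines a cluster by its survey responses. Read together, 18 means respondents.

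It also stands that the protocol undertakes to identify and account for a marked departure from 18, and can keep the survey open longer to reach it. The Discussion acknowledges a possible power limitation for pain/discomfort. None of this repairs the column or the sentence on attrition.

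**Conclusion.** The point holds in three parts of unequal weight.

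1. The attrition column is wrong by its own heading: 412/139/139 should be 453/153/153. This rests only on Table 1 and the stated 30%.
2. For the primary outcome, 18 clusters of 18 responses carry a margin of about 2%, not 30%, so the statement that this recruitment provides for attrition is unsupported. If responses did fall to 12.6 per cluster, power for 4 points would drop by about 7 percentage points on either method (76% to 69%, or 81% to 74%). This assumes ICC 0.05, CV² 0.5625 unchanged by the loss, SD 8.3, 18 clusters retained and a comparison at a single time point. It does not occur if 18 responses are reached at both waves.
3. The 30% is not derivable from the rates quoted beside it, and it is labelled attrition where the design has non-response at each wave. This is a gap in justification, not a demonstrated error.

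A reader should not conclude that extra work groups are required by the 1.3 slip itself, since the inflated column was never used to set the cluster count.

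**What to change.** - In Table 1, replace 412/139/139 with 453/153/153, and say in the text that the clustered N is divided by 0.7.
- Remove the statement that the 18-cluster target provides for attrition. Say instead that 18 clusters of 18 responses give 324 against 317 required for pain/discomfort, which is almost no allowance.
- State the power for 18 clusters at 12.6 responses per cluster beside the power at 18 by the same method, naming the method and its assumptions.
- Describe the 30% as non-response at each anonymous survey wave, and state how it was reached, including the figure taken from the third source.

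The cost is a correction to one table column and a few sentences. The stated figures become less favourable. The correction itself calls for no additional participants or clusters and no change to the design.

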### Analysis

#### Quantitative analysis

The unit for analysis of the primary and secondary outcomes is a cluster (survey responses from a work group). Analysis will be conducted following CONSORT guidelines for cluster-randomised trials [56]. Means for each of the three variables (pain/discomfort score; exposure to physical hazards score and exposure to psychosocial hazards score), at baseline and 12 month follow up, will be generated for each cluster. The mean change by cluster will be calculated by subtracting the baseline from the 12 month follow up score. Analysis will be conducted treating these as continuous variables [63], using a two-sample test, for example a t-test where *n* = total number of clusters, comparing outcomes for the two arms. Data will be cleaned and examined for normal distribution prior to analysis. Differences in cluster sizes will be identified and accounted for using suitable analysis, which will be reported with the results.

The descriptive data will be presented and used when interpreting the results achieved in the work groups. The information collected from wait-list control and intervention work groups about the usual care activities conducted over the 12-month study period, will also provide useful insight to any differences between groups relevant to the analysis.

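### The 80% power in Table 1 belongs to a single-survey, normal-theory comparison, not to the planned cluster-level test of mean change; on 16 degrees of freedom the same inputs give about 75–76%

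*Protocol article*

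**What the plan says.** The Power and sample size section of the protocol article gives its inputs as "taking into account the cluster design at Alpha = 0.05 and Power = 0.80, ICC = 0.05, mean cluster size = 18", together with "mean cluster size = 18 and estimated cluster variation = 0.5625". The Table 1 row for the primary outcome reads "Pain/discomfort 14.9 8.3 4 136 317 412": mean, SD, raw difference, unadjusted N, N after the cluster adjustment, and N after attrition. The effect sizes come from one earlier survey: "The results of a previous study that administered an earlier version of the APHIRM survey to a cohort of workers including paramedics were used". The section gives neither an SD of change nor a correlation between the two surveys. It divides 317 by 18 to reach 18 clusters. For the two hazard outcomes it states "107/18 = 5.9 clusters; in practice three intervention and three control clusters".

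The Quantitative analysis section makes the cluster the unit of analysis. It says "The mean change by cluster will be calculated by subtracting the baseline from the 12 month follow up score" and then "Analysis will be conducted treating these as continuous variables [63], using a two-sample test, for example a t-test where" n is the total number of clusters. It adds that differences in cluster size will be dealt with by a suitable analysis, which it does not name. According to the Abstract and the section on recruitment of survey participants, the surveys are anonymous and go to whoever is eligible in the work group at each wave.

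**The concern.** A power statement should describe the test that will be run. Here the calculation and the analysis differ in two ways. The calculation uses the normal distribution, while a t-test on 18 cluster values has 16 degrees of freedom. The calculation uses the variance of a score at one survey, while the analysis uses the change between two surveys whose respondents cannot be linked.

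The stakes are how a null primary result is read. It would be judged against 80% power for a 4-point difference, which the planned test has not been shown to have. The six-cluster statement could also mislead anyone who adapts the protocol elsewhere, as the Discussion invites readers to do.

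**Working it through.** **Inputs from Power and sample size.** SD 8.3 and difference 4 (pain/discomfort); SD 0.6 and difference 0.5 (hazards); alpha 0.05, power 0.80; ICC 0.05; mean cluster size 18; cluster variation 0.5625. Two assumptions are needed to reproduce Table 1: a two-sided test, and 0.5625 read as the squared coefficient of variation of cluster size.

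**Step 1: reproduce Table 1.**
- Pain/discomfort: n per arm = 2 × 8.3² × (1.960 + 0.842)² / 4² = 67.6, so 68 per arm and 136 in total.
- Hazards: 2 × 0.6² × (1.960 + 0.842)² / 0.5² = 22.6, so 23 per arm and 46 in total.
- Design effect: 1 + 1.5625 × 17 × 0.05 = 2.328.
- 136 × 2.328 = 316.6 (317) and 46 × 2.328 = 107.1 (107).

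All four figures match. An individual-level t-test would have given 138 and 48, so the calculation is normal-theory on single-survey scores.

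**Step 2: keep the standard error and change only the reference distribution.** SE = √(4 × 8.3² × 2.328 / N).

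| N | SE | 4/SE | Power, normal | Power, t with 16 df | Difference detectable at 80% |
|---|---|---|---|---|---|
| 317 | 1.423 | 2.81 | 80.3% | 75.2% | 4.2 |
| 324 (18 × 18) | 1.407 | 2.84 | 81.1% | 76.1% | 4.2 |

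**Step 3: the six-cluster statement.** At N = 107, SE = √(4 × 0.6² × 2.328 / 107) = 0.177 and 0.5/SE = 2.82. Power is 81% by normal theory but 57% with 4 df. At N = 324, SE = 0.102, 0.5/SE = 4.92, and power with 16 df is over 99%.

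**Step 4: the change score.** Differencing two surveys multiplies the variance of a cluster value by 2(1 − ρ), where ρ is the correlation between a cluster's two means. The variance falls if ρ exceeds 0.5 and rises if it is smaller. With the design effect of 2.328, 80% power on 16 df needs ρ of about 0.55. The protocol gives no ρ.

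To show the range, take the variance of a cluster mean change as 2 × SD² × [ICC(1 − CAC) + (1 − ICC)(1 − f)/m]. CAC is the cluster autocorrelation, f is the share of repeat respondents times the within-person correlation, and m is 18 responses at each wave. CAC and f are assumptions, not protocol figures. For unequal sizes, the factor 1.5625 multiplies the respondent term in an unweighted analysis (lognormal sizes) and the cluster term in a size-weighted one.

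Two examples with f = 0:
- CAC 1, equal sizes: 2 × 68.89 × 0.95/18 = 7.27; SE = √(2 × 7.27/9) = 1.271; 4/SE = 3.15; power 84%.
- CAC 0, unweighted: 2 × 68.89 × (0.05 + 0.95 × 1.5625/18) = 18.25; SE = 2.014; 4/SE = 1.99; power 46%.

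Power (%) with 16 df at CAC 0 / 0.5 / 0.8 / 1:

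| f | Unweighted | Size-weighted | Equal clusters of 18 |
|---|---|---|---|
| 0 | 46 / 55 / 61 / 66 | 47 / 61 / 74 / 84 | 56 / 68 / 77 / 84 |
| 0.25 | 53 / 64 / 72 / 78 | 51 / 68 / 82 / 93 | 62 / 76 / 86 / 93 |
| 0.5 | 61 / 75 / 85 / 92 | 56 / 76 / 91 / 99 | 69 / 85 / 95 / 99 |

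Simulation of the unweighted and equal-size cases agreed to within about two percentage points.

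**The case against.** The best defence is that the protocol does not fix the analysis closely enough for its power to be called low. The t-test is only an example, and the article commits to accounting for unequal cluster sizes, so an unweighted comparison is one option and not the plan. Differencing also removes stable differences between stations, and staff who answer both surveys reduce the variance even though their records cannot be linked. This stands, and it rules out a stronger reading that a reader might draw: that anonymous change scores and small stations necessarily push power well below 80%. The documents do not support that, because the direction depends on a correlation they do not give.

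Two further points carry some weight. The article says "A conservative approach was taken by choosing a flat intra-cluster correlation coefficient (ICC) of 0.05"; on the same single-survey basis with N = 324 and 16 df, power would be 81% at an ICC of 0.04 and 91% at 0.02. The Discussion also concedes a possible shortage of power for pain/discomfort. But 0.05 is the ICC on which the 80% is stated, and the concession gives no figure and leaves Table 1 unchanged.

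Finally, the six-cluster error does no harm to this trial, which enrols 18 clusters for every outcome. That is correct, and it makes the point one of wording. Deferral to an analysis plan does not answer the main point, since the article itself states both the calculation and an analysis that does not match it.

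**Conclusion.** Wrong as written. The degrees-of-freedom step uses only the protocol's inputs and its example test: about 75–76% power in place of 80%, and a detectable difference of about 4.2 points in place of 4. The six-cluster statement corresponds to about 57% power.

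Beyond that there is only a range. For mean changes with no repeat respondents, power is roughly 46–84% across cluster autocorrelation from 0 to 1 and the choice of weighting. With enough respondent overlap, or size weighting combined with a high autocorrelation, it reaches 80% or more. These figures assume a mean of 18 responses per cluster at both waves. The protocol therefore does not show that the planned test has 80% power, but nor can one conclude from it that the trial is clearly underpowered.

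**What to change.** Restate power and detectable difference for the cluster-level analysis of mean change. Use the t distribution on the residual degrees of freedom, sampling error from both surveys, the stated cluster-size variation with the intended weighting, and an explicit range for the between-wave correlation. Show the degrees-of-freedom correction on its own (about 75–76%, 4.2 points) so that readers can see what does not depend on that correlation. Delete the statement that six clusters suffice for the hazard outcomes, or restate it as about 57% power, and note that 18 clusters give over 99% on the single-survey basis.

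The cost is a short recalculation, a few lines of text and a less favourable stated power. The correction needs no extra clusters and no change to the conduct of the trial.

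### The 18 clusters come from the pre-attrition N of 317, so for pain/discomfort they do not contain the 30% attrition allowance that the protocol says they do

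*Protocol article*

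**What the plan says.** All of this stands in the protocol article under *Power and sample size*. The design inputs are "Alpha = 0.05 and Power = 0.80, ICC = 0.05, mean cluster size = 18 and estimated cluster variation = 0.5625". For pain/discomfort, Table 1 gives an SD of 8.3, a difference of 4 points, and three sample sizes: 136 without clustering, 317 with it, and 412 after 30% attrition. For each of the two hazard outcomes the figures are 46, 107 and 139.

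The text below the table introduces these numbers with "The required sample size for the intervention arm, accounting for this cluster design was calculated", and says that 30% was then added for loss at the 12-month follow-up. The number of clusters for the primary outcome is given as "317/18 = 17.6 clusters; in practice, nine intervention and nine control clusters". The paragraph closes with the aim of recruiting 18 clusters "of 18 or more participants from one region of the organisation to allow for potential attrition".

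**The concern.** The plan works out an attrition-adjusted N and then does not use it. The division that fixes the number of clusters starts from 317, the figure before attrition, while the closing sentence describes the result as if attrition were covered. The two statements cannot both hold for the primary outcome.

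In addition, the N is described as that of the intervention arm, yet it is split over nine intervention and nine control clusters. A reader who takes the label literally would conclude that the trial needs twice as many people as the calculation supports.

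At stake is how the primary result is read. The article states 80% power with attrition allowed for. If the assumed attrition occurs, a null result on pain/discomfort would be judged against a power figure that the planned cluster count does not support.

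**Working it through.** **Inputs, all from *Power and sample size* and Table 1.** Alpha 0.05 (taken as two-sided, which reproduces the table), power 0.80, ICC 0.05, mean cluster size m = 18, cluster variation 0.5625, SD 8.3, difference 4, attrition 30%, k = 18 clusters.

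**Reproducing the plan's figures**

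- Unclustered total: 4 × (1.96 + 0.8416)² × (8.3/4)² = 135.2. Rounding up per arm gives 68, so 2 × 68 = 136. This matches Table 1 and shows that 136 is the total for two arms.
- Design effect: 1 + {[1 + CV² × (k − 1)/k] × m − 1} × ICC. With CV² = 0.5625, this is 1 + {[1 + 0.5625 × 17/18] × 18 − 1} × 0.05 = 2.328.
- Clustered total: 136 × 2.328 = 316.6 (stated 317). Secondary outcomes: 46 × 2.328 = 107.1 (stated 107).
- The value 0.5625 has to be the squared coefficient of variation. Read as the coefficient itself it gives about 290, and equal clusters give about 252; neither matches 317.
- Attrition: 317 × 1.3 = 412.1 (stated 412) and 107 × 1.3 = 139.1 (stated 139).

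**Carrying the plan's own attrition-adjusted N forward**

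| Outcome | N before attrition | ÷ 18 | N after attrition | ÷ 18 |
|---|---|---|---|---|
| Pain/discomfort | 317 | 17.6 | 412 | 22.9 |
| Each hazard outcome | 107 | 5.9 | 139 | 7.7 |

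The planned 18 clusters of 18 give 324, which is 7 above 317 and 412 − 324 = 88 below 412. For pain/discomfort, 412 needs 23 clusters of 18 (24 for equal arms), or 18 clusters averaging 22.9. For the hazard outcomes, 18 clusters are well above 7.7.

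**Power for 4 points with 18 clusters**

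Thirty per cent loss within each cluster leaves 18 × 0.7 = 12.6 per cluster, or 226.8 (about 227) in all. The same formula at m = 12.6 gives a design effect of 1.915. The standard error of the difference is 8.3 × √(4 × design effect / N).

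| | No loss (m = 18) | 30% loss (m = 12.6) |
|---|---|---|
| N analysed | 324 | 227 |
| Design effect | 2.328 | 1.915 |
| Standard error | 1.407 | 1.525 |
| Power, normal approximation | 81% | 75% |
| Power, t-test on 16 df | 76% | 69% |
| Difference detectable at 80%, normal | 3.9 | 4.3 |
| Difference detectable at 80%, t-test | 4.2 | 4.6 |

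The t-test rows are shown because *Quantitative analysis* makes the cluster the unit and gives a t-test on the number of clusters as its example; 18 clusters leave 18 − 2 = 16 degrees of freedom. Attrition costs about 6 to 7 percentage points on either scale. The further 5 to 6 points between the two power rows come from the choice of test, not from attrition.

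**The case against.** The strongest reply is that this is not a closed cohort losing members. According to the *Abstract*, the 12-month survey goes to all current eligible staff, so leavers can be replaced. *Recruitment of survey participants* counts the 18 in survey responses and lets the survey stay open longer to reach it. The 30% was itself drawn partly from survey response rates, so deducting it from 18 responses may count non-response twice. If about 18 responses per cluster come back at 12 months, the plan's formula gives 81%. This stands, and it makes the power loss conditional. It does not rescue the text: the plan does not make this argument, but sets attrition at 30%, applies it to the follow-up and says that it is covered.

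Secondly, 18 is worded as a minimum, and some stations have more than 40 eligible staff, so 18 clusters could reach 412. But the same section sets 18 as the expected mean, and the survey procedure treats it as the target; nothing plans for 22.9.

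Thirdly, the *Discussion* acknowledges a possible limitation in power for pain/discomfort, and *Power and sample size* says that a marked departure from a mean of 18 will be taken into account. Both soften the consequence, but neither gives a figure or corrects this step.

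Lastly, the attrition statement is correct for the secondary outcomes. That is so, and it should be kept for them.

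**Conclusion.** The point holds for the primary outcome. The cluster count rests on 317, the 412 is never used, and the statement that 18 clusters of 18 or more allow for attrition is untrue for pain/discomfort. The label that ties the N to the intervention arm is also wrong, since 136 and 317 are totals for both arms.

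The size is moderate. At the plan's own 30% loss, power falls from 81% to about 75% by the normal approximation, with a detectable difference of about 4.3 points. On the 16-df t-test it falls from about 76% to about 69%, with the detectable difference rising from about 4.2 to about 4.6 points. These figures assume that the loss is spread evenly within clusters, that cluster-size variation is unchanged, and that the ICC and SD are as stated. The SD of 8.3 is cross-sectional, whereas the planned analysis compares changes in cluster means, so the figures restate the plan's calculation and are not a power derived for that analysis.

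A reader might infer that the trial cannot reach 80% power, or that it must add clusters. The documents support neither: on the plan's formula 80% is met if about 18 responses per cluster are obtained again. A reader might also blame attrition for the whole drop to 69%; part of it is the test.

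**What to change.** In *Power and sample size*, below Table 1:

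1. State that 18 clusters of 18 (324) meet the primary-outcome N only without loss, that is, if about 18 responses per cluster are obtained again at 12 months.
2. Restate primary power for 4 points at 30% loss as about 75% (normal approximation) or 69% (16-df t-test). Put the no-loss figures of 81% and 76% alongside, and note that all use the cross-sectional SD of 8.3. Give the matching detectable differences at 30% loss: about 4.3 and 4.6 points.
3. Limit the statement that 18 clusters allow for attrition to the two secondary outcomes.
4. Describe the N as that for both arms combined instead of for the intervention arm.

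The cost is wording only. No clusters are added, and randomisation, outcomes and analysis are unchanged, so it can be done with recruitment under way. The price is a less favourable stated power for the primary outcome.
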